#### *Primary and Secondary Outcomes*

The primary outcome will be **clinical malaria**, defined (according to WHO criteria) as parasitemia (malaria parasites detected on a blood smear) of any density plus history of fever (within 48 hours) or axillary temperature  $>37.5^{\circ}\text{C}$ . Criteria for clinical malaria will be taken from the UNICEF Case Management Series, entitled, "Promoting Rational Use of Drugs and Correct Case Management in Basic Health Services – Malaria Prevention and Treatment" published by UNICEF's Programme Division in cooperation with the World Health Organization in 2000. To distinguish unique malaria episodes, treatment will be supervised and follow-up blood smears will be collected from the child as described below in Section 5.2(c).

Secondary outcomes will include: (i) changes in anemia status; (ii) the severity of the clinical malaria (based on level of parasitemia); (iii) cerebral malaria; (iv) hospitalization (from any cause) (v) death; (vi) pneumonia; (vii) diarrhea and dehydration.

*Subjects/study population*

Infants and young children (6-24 months of age), living in the Brong Ahafo Region of northern Ghana, will be included in the study if, at baseline, they are ingesting weaning foods in addition to breastmilk; free from malaria or other major illness; afebrile; living in the study area for the duration of the intervention and follow-up period; and if parental consent is obtained. Inclusion of a child into the study will proceed after the possible risks and benefits are discussed with the parents (in the appropriate local language), and a signed consent is obtained. The exclusion criteria are as follows: severe anemia (hemoglobin <70g/L), weight-for-height <-3 z-score (severe wasting), kwashiorkor (defined as evidence of edema), congenital abnormality, treatment with iron supplements in the past 6 months, or any chronic illness. Children that are severely anemic (Hb<70 g/L) and/or have symptoms of clinical malaria will be excluded from entry to the study and referred to the local health provider for treatment according to Ghana Ministry of Health guidelines.

*Sample Size*

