| 0.15                 | 3.44 | 0.75                   | 2.58    | 2.97  | 351   | 0.42     | 843 | 0.15       | 970             |
| 0.2                         | 3.44        | 0.75                          | 2.58           | 3.10         | 202          | 0.42            | 485        | 0.15              | 558                    |

\*Adjusted for estimated bed net use and loss to follow-up

**5.2 Procedures***Recruitment, Randomization Process and Blinding*

Subjects will be recruited from villages in the Kintampo Health Research Centre (KHRC) study area once permission has been obtained from the village assemblies and elders, as well as the parent or guardian of the eligible child. Field researchers, employed by the KHRC, will visit individual households/compounds and interview parents or caregivers regarding the inclusion criteria. Once consent has been obtained and documented via signature or thumbprint, eligible children (one per household/compound) will be enrolled and randomized, using a computer-generated model, to either the iron (Fe) or placebo (P) group.

Sachets containing the powdered minerals with and without iron will look and taste identical with the exception that each package will be marked with an 'A' or 'B' denoting packages with or without iron. The study team and caretakers of children will be blinded to the 'A' or 'B' designation. Only the manufacturer of the powdered fortificant (in Ghana) and a research pharmacist each in Toronto and Kintampo will hold the key to the randomization and 'sachet' code lists. The key will be revealed to the 'Data and Safety Monitoring Committee (DSMC)' at the end of the first phase if a significant difference in outcomes is observed, and to the researchers after the database is closed and statistical analyses completed.

*Supply and content of the powdered mineral and vitamin fortificant.*

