a) *Baseline:* After consent is provided, subjects will be screened for anemia (based on hemoglobin) and parasitemia. Enough blood will be taken to determine ferritin (SF), C-reactive protein (CRP), serum transferrin receptor (TfR) and zinc protoporphyrin (ZnPP). Those who are severely anemic (Hb <70 g/L), or have clinical signs of infection (including malaria) will be referred to the study clinician who will offer the child the standard care, as defined by the Ghana Ministry of Health. All other children will be enrolled and randomized to either the iron (Fe) or placebo (P) group. The child's weight and length measurements will be recorded, as well as any relevant demographic (age, gender) and historical health information (birth weight, immunization status, and previous hospitalizations). Caregivers will also be asked to provide information regarding their usual feeding practices and health-seeking behaviours. All households will be provided with a treated bed net and a supply of powdered fortificant with oral instructions on how to use each.

*b) Monitoring visits:* Field researchers will visit each subject at their home every week in the first month of the study and at 4 week intervals for the next 4 months. At each visit, the field researcher will conduct a health assessment (including axillary temperature) and collect information on feeding history, supplement compliance, bed net use and morbidity. At the initial weekly visits, 7 new sachets will be provided, and then at the start of the second month, 30 new sachets will be provided to last for a month. Clear instructions for storage and administration of sachets will be provided to families. All used and unused sachets will be counted and recorded. It has been our experience in other similar studies in Ghana and elsewhere that by providing pre-emptive information on the impact of the fortificant to parents (like telling parents that stools will darken from the iron, and that children will become more active and have enhanced appetites), the adherence to the use of the sachets is generally in the range of 70 – 98%. We will provide this pre-emptive information in the current study.

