## **5.8 Potential Difficulties and Limitations**

a) Blinding: Although research staff will be blinded to the intervention, the stools of children receiving the iron containing fortificant will likely be darker (blackier) than those receiving the placebo. The applicants are unable to control for this likelihood.

b) If after the first phase (the dry season) there is more clinical malaria or more severe malaria or health complications in the group receiving the iron-containing fortificant, the DSMC may recommend terminating the study before the second phase begins.

c) It will not be possible to compare the results of the proposed current study to many of the results from the Pemba study. In Pemba, the primary outcome was mortality, which necessitated a sample size of more than 30,000 subjects. Also, in the current protocol, folic acid will not be included in the powdered mineral and vitamin supplement. Based on the estimated dietary folic acid intake of older infants and children in West Africa, folic acid deficiency should not be a problem (fruit is plentiful and inexpensive). Lastly, in the current protocol all children will receive and be encouraged to use bed-nets. This was not the case in the Pemba study.

d) Although studies in adults have suggested that elevations in TfR (82) or in ZnPP (75) can be definitive indicators of iron deficiency, there is large overlap in the distributions of these indicators in children with iron deficiency anemia as well as those with normal iron status. This overlap may be explained by a greater variability in the erythroid mass in children than in adults (83) together with the many variables affecting children in developing countries that influence TfR and ZnPP independent of iron status. Because of this overlap, the sensitivity and specificity of TfR and ZnPP in identifying iron deficiency and IDA may not be as high as we would prefer regardless of the diagnostic cutoffs chosen. Despite this limitation, all three biomarkers of iron status, ferritin, TfR and ZnPP, will be statistically evaluated individually and in groupings since this measure is very important in the context of the current study.

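### The planned counselling tells caregivers that dark stools come from the iron, which hands them the key to an allocation they are meant not to know

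*Protocol*

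**What the plan says.** Section 5.2 (Recruitment, Randomization Process and Blinding) states: "The study team and caretakers of children will be blinded to the 'A' or 'B' designation". Sachets look and taste alike, but "each package will be marked with an 'A' or 'B' denoting packages with or without iron", so there is one letter per arm.

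Section 5.2 (Clinical protocol, b, Monitoring visits) describes advance information for parents, namely "telling parents that stools will darken from the iron, and that children will become more active and have enhanced appetites". It credits this kind of information with adherence of 70–98% in similar studies and adds: "We will provide this pre-emptive information in the current study". It makes no distinction by arm.

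Section 5.8(a) says that "the stools of children receiving the iron containing fortificant will likely be darker (blackier) than those receiving the placebo", and then: "The applicants are unable to control for this likelihood".

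Section 5.1 defines the primary outcome as parasitemia "of any density plus history of fever (within 48 hours) or axillary temperature" above 37.5°C. Under section 5.2 (c, Tracking the subjects), a blood sample is taken when a fever has been reported or recorded, and ill children are identified when they visit a health facility. The primary analysis in section 5.5 compares the upper 95% confidence limit of the incidence ratio with a 10% tolerance limit.

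**The concern.** Stool colour is the one visible sign expected to differ between the arms. The darkening itself cannot be prevented, but explaining its meaning to caregivers is a choice. A mother who sees dark stools and has been told they come from iron can infer her child's arm. A mother who sees no change can infer the opposite, and for her the stool message was untrue. With one letter per arm, a child whose arm has been worked out can also reveal the arm of other children whose sachets carry the same letter.

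This matters because the trial asks whether iron raises malaria incidence, and a case is usually counted only after someone reports a fever or brings the child in. Caregivers who believe they know the arm may report more or less readily, and the comparison against a 10% limit leaves little room for such a difference.

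**Working it through.** **1. The passages side by side.** Blinding of caretakers is promised (5.2, Recruitment). All parents are to be told that iron darkens stools (5.2, Clinical protocol b). Iron-arm stools are expected to be darker than placebo stools (5.8a). Together these give the caregiver both the sign and its meaning. Section 5.8(a) discloses the sign only.

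**2. How much detection rests on caregivers.** Home visits with axillary temperature are weekly in month 1 and then 4-weekly for four months: 4 + 4 = 8. Assume each visit covers 2–3 days of fever (the 48-hour history plus the visit day). Over about 152 days:

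- 8 × 2 / 152 = 10.5%
- 8 × 3 / 152 = 15.8%

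So roughly 11–16% of follow-up is covered by scheduled visits. The extra contacts for smears on days 3, 7, 14 and 28 after a treated episode are not counted, so true coverage is somewhat higher.

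**3. The plan's own sample size.** From section 5.1 and Table 1: rate 3.44 × 0.75 = 2.58 per child-year without iron, 2.58 × 1.15 = 2.967 with iron, 80% power. Person-years per group = (z_α + z_β)² (r0 + r1)/(r1 − r0)². With two-sided 0.025 (5% halved for two tests):

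(2.241 + 0.842)² × 5.547 / 0.387² = 352.0, against 351 stated.

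Then 351/(5/12) = 842.4, given as 843, and 843 × 1.15 = 969.5, given as 970 per group. The figure reproduces, and Table 1 treats 351 as per group in one season.

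**4. Illustration of a reporting difference.** Let the observed ratio be RR = true ratio × relative reporting (iron/placebo). With Poisson variance only,

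SE(log RR) = √[1/(2.58 × 351) + 1/(2.58 × RR × 351)],

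P(upper 95% limit < 1.10) = Φ{[log 1.10 − log RR]/SE − 1.96}.

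For a true ratio of 1.10, where concluding non-inferiority is an error:

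| Iron-arm reporting | Observed RR | SE | P(false non-inferiority), one season |
|---|---|---|---|
| no difference | 1.100 | 0.0459 | 2.5% |
| 1% less | 1.089 | 0.0460 | 4.1% |
| 2% less | 1.078 | 0.0461 | 6.4% |
| 5% less | 1.045 | 0.0465 | 19.6% |

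If 11–16% of cases are found actively and are free of the bias, the 5% row becomes RR = 1.10 × (0.11 + 0.89 × 0.95) = 1.051, giving 16.4%, to RR = 1.10 × (0.16 + 0.84 × 0.95) = 1.054, giving 15.0%.

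In the other direction, with a true ratio of 1.00 and 5% more reporting in the iron arm, the chance of showing non-inferiority falls from 52.7% to 16.9% (20–21% with the same allowance for active detection).

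The shifts of 1%, 2% and 5% are assumptions. Nothing in the protocol fixes their size or sign.

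**The case against.** The strongest reply is that section 5.8(a) already discloses darker stools, and that colour would unblind some caregivers whatever they were told. That is true. The sentence saying the applicants cannot control this refers to the stools and remains correct. It does not cover the counselling, which is within their control and is not mentioned there.

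The outcome also has objective parts: a positive slide read by two independent microscopists with a third for disagreements, temperature taken at home visits, and repeated study contact after each treated episode. At 2.58 per year that is 2.58 × 5/12 ≈ 1.1 episodes per child. This stands as a limit on the size of any bias. It does not remove the caregiver's part in the first report of a fever between visits.

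The information serves adherence, and lower adherence would itself dilute any harm of iron. This is a reason to keep reassurance, not to attribute stool colour to iron. The stool text is phrased as an example from earlier studies, but the next sentence commits to it here.

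A reader might go further and infer that the script unblinds field staff. The protocol does not say who gives the message or that staff inspect stools, and the applicants already know that iron darkens stools. A reader might also infer that parents are told iron raises malaria risk. Section 8.2a says only that risks and benefits are explained, section 8.1c lists possible risks in both arms, and the consent pages are not shown. Nor can the activity and appetite message be called false for the placebo arm, which receives zinc and vitamins A and C.

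**Conclusion.** The conflict is established by the text: a trial that promises blinded caretakers commits to telling them what the distinguishing sign means, and its stated limitation omits this avoidable part. Detection between visits leans enough on caregivers for the conflict to reach the primary outcome.

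The size of the consequence is not established. The 4%, 6% and 20% figures (15–16% in the last case after allowing for active detection) rest on assumed reporting shifts, the planning rate, Poisson variance and 351 person-years per group. They show sensitivity to small shifts, not an expected bias. It would be tempting to charge the whole shift to the script, but some would occur from colour alone and the share due to the wording cannot be identified. This is an inexpensive protection of blinding that should be adopted, not evidence that the result would be biased.

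**What to change.** - In section 5.2 (Clinical protocol, b), use one identical message for both arms that does not name iron as the cause of stool changes and keeps general reassurance to support adherence. For example: *stool colour may or may not change while using the sachets; this is harmless*.
- At the existing 5-month visit (section 5.2, Follow up), record the caregiver's and the field worker's guess of allocation.
- In section 5.8(a), keep the limitation and add that counselling will not link stool colour to iron and that blinding will be assessed.

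Restricting the analysis to measured fever would not repair the problem, because the child must still be brought in. Restricting it to home-visit cases would leave about 906 × 0.11 to 906 × 0.16, or 100–145, events per arm per season, with about 10–13% power at the 10% limit if iron is harmless.

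The cost is a reworded script and two questions at a visit already planned. The downside is slightly less specific reassurance for mothers in the iron arm.

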*c) Follow up:* At the end of 5 months, subjects will again be screened for anemia, ferritin, CRP, serum transferrin receptor, zinc protoporphyrin and a blood smear for their malaria status. The subjects will be weighed and measured, and caregivers will again be asked about feeding history, supplement use, and bed net use. Any remaining sachets will be collected and counted. All families that have completed the intervention will be provided with a study closure package (including some rice and soap) as has been the standard goodwill practice of KHRC to participants from the communities. For those children who are anemic, based on their end-line hemoglobin assessment, an additional 60 sachets of iron-containing powdered fortificant will be provided. Providing iron to anemic children is not a safety issue in this case because they will be eligible for treatment according to the WHO statement on the use of iron in malaria endemic areas (3).

*d) Discontinuation of supplementation.* Supplementation will be stopped if any of the following is reported: admission to the hospital ward for >5 days; evidence of chronic diarrhea (defined as loose stools lasting >4 weeks); prolonged fever of unknown origin; emergence of any exclusion criteria after randomization. Prompt, daily disclosure by field workers of any concerns will be encouraged. If necessary, children will be referred to local physicians for treatment according to local standards. Reasons for stopping supplementation voluntarily will be recorded.

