Zimmerman et al recently studied the use of serum transferrin receptor and zinc protoporphyrin as indicators of iron status in African children (Côte d'Ivoire). He determined the most sensitive and specific markers for iron status and their 'optimal' diagnostic cutoffs (TfR  $>9.4$  mg/L or ZnPP  $> 52$   $\mu\text{mol/mol}$  heme) after correcting for

inflammation (79). We plan to use these cutoffs to define iron status as iron replete and anemic, iron deficient and anemic, of iron replete and not anemic. Zimmerman defined anemia as a hemoglobin concentration below the WHO cutoff values (110 g/L) minus 10 g/L, and normal ferritin as  $> 30 \mu\text{g/L}$  (79). Several investigators have argued that a SF concentration  $>30 \mu\text{g/L}$  should be used to define adequate iron stores in developing countries with a high prevalence of infection (63, 80). Therefore, we have chosen a SF cutoff of  $>30 \mu\text{g/L}$  as being indicative of iron sufficiency.

To summarize: anemia will be defined as  $\text{Hb} < 100 \text{ g/L}$ ; IDA will be defined as  $\text{Hb} < 100 \text{ g/L}$  plus one of low ferritin ( $<30 \mu\text{g/L}$ ), high TfR ( $>9.4 \text{ mg/L}$ ) or ZnPP ( $>52 \mu\text{mol/mol heme}$ ); and iron deficiency will be defined as one of low ferritin ( $<30 \mu\text{g/L}$ ), high TfR ( $>9.4 \text{ mg/L}$ ) or ZnPP ( $>52 \mu\text{mol/mol heme}$ ). We recognize that infection and inflammation will confound the interpretation of SF, TfR, and ZnPP; thus we will exclude and/or adjust these indicators for those children who have signs of infection or inflammation, as defined by an elevated CRP concentration ( $>8 \text{ mg/L}$ ) (55, 81).

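### The end-line supply of 60 iron sachets has no lower hemoglobin limit, so as written it covers children below 70 g/L without the referral the protocol requires for them at baseline

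*Protocol*

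**What the plan says.** Section 5.2, c) Follow up, describes the visit at five months. Hemoglobin and iron markers are measured and a smear is taken, and then: "For those children who are anemic, based on their end-line hemoglobin assessment, an additional 60 sachets of iron-containing powdered fortificant will be provided". The reason given is that "Providing iron to anemic children is not a safety issue in this case", with reference to the WHO statement on iron in malarious areas. The supply comes as participation closes: "All families that have completed the intervention will be provided with a study closure package".

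Four other places deal with the same hemoglobin scale.

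- Section 5.3, Laboratory and Clinical Analyses, summarizes its definitions with "To summarize: anemia will be defined as" hemoglobin below 100 g/L. No lower bound is given.
- Section 5.1, Subjects/study population: "The exclusion criteria are as follows: severe anemia (hemoglobin <70g/L". These children are referred to the local health provider.
- Section 5.2, a) Baseline: "Those who are severely anemic (Hb <70 g/L), or have clinical signs of infection (including malaria) will be referred to the study clinician", who offers Ministry of Health standard care.
- Section 5.2, d) Discontinuation, lists among the reasons for stopping supplementation "emergence of any exclusion criteria after randomization". It then allows referral to local physicians where this is judged necessary.

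**The concern.** A hemoglobin below 70 g/L is a trigger for clinical referral on the first day of the study. On the last day, the only written action for the same result is to send sachets home. Section 5.2 schedules no later contact, apart from the smears for children under treatment for malaria. At one sachet a day the supply lasts 60 days.

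A finding of severe anemia could therefore be made at the last visit without any rule that a clinician sees the child. Anemia at that level can have causes that iron does not address, which is a reason for clinical review whether or not iron is also given. The stake is participant safety after the final assessment. The analysis is not involved.

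**Working it through.** No power, alpha or event figure bears on this, so the check sets the rules side by side for one hemoglobin value, below 70 g/L.

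| Time point | Protocol section | Action for Hb <70 g/L |
|---|---|---|
| Eligibility | 5.1 | Excluded and referred, automatic |
| Baseline | 5.2(a) | Referred to the study clinician, automatic |
| During the intervention | 5.2(d) | Supplementation stops; referral discretionary |
| End-line | 5.2, c) Follow up, with 5.3 | 60 iron sachets; no referral stated |

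**Step 1. Who receives the sachets.** Paragraph (c) says anemic children. Section 5.3 sets anemia at Hb <100 g/L. Every value below 70 is also below 100, so severely anemic children fall within the rule.

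**Step 2. Whether another rule takes them out.** Paragraph (d) is the only candidate. It governs stopping the trial supplement. The sachets in (c) are a new supply given when the intervention is over, and (c) does not refer to (d). If (d) is nevertheless read as applying at end-line, it withholds supplementation from a child to whom (c) gives it. On that reading the two paragraphs contradict each other. On the other reading the child below 70 g/L has no separate rule. The text needs correcting either way.

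**Step 3. Whether the result would already have been found.** Monitoring visits are weekly in the first month and then "at 4 week intervals for the next 4 months". Their listed content is a health assessment with axillary temperature, feeding, compliance, bed net use and morbidity. Hemoglobin is not on the list. End-line is therefore the only scheduled post-baseline measurement, and the main point at which hemoglobin newly below 70 g/L would be detected.

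**Step 4. Whether such children could exist.** Entry admits children from 70 g/L upward. Section 3.1 cites a study in which average hemoglobin fell over the malaria season, and the second cohort is followed through the wet season. This shows that the group need not be empty. It gives no rate.

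**Step 5. Scale.** The protocol gives no proportion below 70 g/L at end-line. As a conversion only, take the planned 1,940 children per cohort and the planned 15% loss:

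- 1,940 × 0.85 = 1,649 children at end-line per cohort
- 0.01 × 1,649 = 16.5, so each one percentage point is about 16 children per cohort

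This is not an estimate of how many would be affected.

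**The case against.** The strongest reply is that the protocol does provide for these children, though not in this paragraph. Section 8.2b describes an established clinical facility and referral system, mentions complicated anemia by name, and says that the system will be open to every child in the trial. Paragraph 5.2(d) can be read as the exception for severe cases, with (c) as the general rule. Section 8.5 promises a detailed safety monitoring plan that is not at hand. Paragraph (c) also does not say that sachets replace care. Finally, the baseline rules govern entry to a trial in which half the children receive no iron, so excluding severely anemic children from randomization does not imply that iron is wrong for them.

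Much of this stands. It shows that referral is feasible and that nothing forbids it. It does not supply a trigger: section 8.2b names no hemoglobin value, and (d) leaves referral to judgment, whereas baseline makes it automatic.

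A reader might infer more than the text supports:

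- **That the sachets would harm severely anemic children.** The protocol contains no evidence of this, and standard care may itself include iron.
- **That these children are left to die untreated.** Section 8.4 speaks of untreated severe iron deficiency anemia, not of every hemoglobin below 70 g/L. A child with iron deficiency would at least receive iron from the sachets.
- **That the appeal to the WHO statement is itself an error.** Section 2 does say that the statement made no recommendation on powders, but that is not a prohibition. The conditions quoted in section 3.1 are largely met: all households receive treated nets, malaria is managed under national guidelines, and section 2 puts iron deficiency anemia as high as 60–65% in children under 24 months in West Africa.
- **That malaria at end-line goes unchecked.** A smear is taken at that visit, and section 5.3 provides for rapid tests to guide treatment.

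**Conclusion.** The point holds as an inconsistency in a stated clinical rule. As written, the end-line supply includes children below 70 g/L and requires no referral. Baseline refers the same value automatically, and 5.2(d) treats it as a reason to stop supplementation. The discretionary referral in (d) and the facilities in section 8.2b soften the gap but do not close it.

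The conclusion rests on the literal definition of anemia in section 5.3 and on the listed content of the monitoring visits. It needs no assumption about how many children are affected, which cannot be derived from the protocol. Trial inference is untouched, because the supply follows the final assessment. The correction should be made: it concerns participant safety and costs almost nothing.

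**What to change.** In section 5.2, c) Follow up, limit the supply of 60 sachets to children with end-line hemoglobin of 70 to below 100 g/L. Add that every child below 70 g/L is referred to the study clinician for Ghana Ministry of Health standard care, which may include iron, as in 5.2(a).

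This is one sentence. It uses a measurement already taken and a referral route already in place. The downside is that a few children may need one more contact and receive iron slightly later. No change to the malaria testing or to the sentence citing the WHO statement is needed for this point.
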